### Study Aims

This prospective cohort study aims to evaluate the effectiveness of a comprehensive Internet-based intervention targeting student MSM attending university. Specifically, it seeks to assess the intervention’s impact on reducing HIV-related high-risk behaviors and lowering the prevalence of HIV and other STIs within this population, using a before-and-after controlled trial design.

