### Study Design

The study evolved from a 2024 local public health intervention pilot. During the ethical review in June 2024, the local ethics committee recommended that, given the sensitivity and vulnerability of university student participants, all eligible students should receive access to the intervention resources and that establishing a nonintervention control group would be ethically inappropriate. Considering this recommendation and the small, hard-to-reach population size, a randomized controlled trial was deemed infeasible. Therefore, a before-after self-controlled cohort design was adopted, allowing participants to serve as their own controls to assess within-person changes.

Guided by findings from systematic reviews indicating that a 12-month intervention period is optimal for achieving behavioral changes [14], this study will set a 12-month intervention duration, with an interim follow-up assessment at 6 months.

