### Study Population

#### Inclusion Criteria

Participants will be eligible for inclusion if they meet all of the following criteria: (1) male, aged 18 years or older; (2) currently enrolled university student (including students pursuing technical diplomas or undergraduate degrees); (3) self-identified MSM, defined as having engaged in sexual behaviors with men, including mutual masturbation, oral sex, or anal intercourse; (4) confirmed HIV-negative status at baseline screening; and (5) willing and able to provide written informed consent to participate in the study.

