#### Sample Size

To estimate the required sample size for a prevalent cohort under an exponential distribution assumption, we adopted the 2-sample Poisson rate comparison framework described by Shiue and Bain [15]. Detailed formulas and derivations are provided in Multimedia Appendix 1.

We assumed a baseline HIV incidence of 4 per 100 person-years (estimated from multiple MSM cohort studies in China [16-18]) and an expected postintervention incidence of 1 per 100 person-years (a 75% relative reduction), with a 2-sided α of .05, 80% power, and an anticipated 10% attrition over 12 months. Based on these assumptions, the required sample size is 484 participants.

The projected reduction to 1 per 100 person-years (75%) was empirically derived. Continuous surveillance of the MSM population in Chengdu observed a 60.9% year-over-year decline in new HIV infections between 2022‐2023 and 2023‐2024 (internal monitoring data available upon request). Building upon this trend, our multilevel intervention—integrating digital education, peer counseling, and PEP subsidies—is expected to produce further improvement. Preexposure prophylaxis (PrEP) combination-prevention intervention internationally has achieved 31.5% relative risk reduction among MSM [19], thus a 75% reduction was adopted as an empirically grounded upper-bound planning scenario.

We anticipated a 12-month retention rate of approximately 90% in this online cohort of student MSM. This assumption is informed by previous longitudinal studies among young men who have sex with men and gay/bisexual men, which have reported 12-month follow-up retention of 85% to 91% under structured follow-up procedures and supportive engagement strategies [20,21]. Given that our study uses multiple retention strategies (scheduled online follow-ups, advance notification of all incentive payments at enrollment, and close coordination through student volunteers), a 10% loss to follow-up was considered an ambitious but achievable design target. Sensitivity analyses at 25%, 50%, and 75% relative reductions and attrition rates of 10% to 20% were prespecified at the fixed N to assess feasibility and robustness (see Multimedia Appendix 2 for summary scenarios).

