#### Recruitment via Blued

Additional recruitment will be conducted through Blued, a popular location-based social networking application specifically designed for MSM, developed by BlueCity Holdings (Beijing, China). Student volunteers will create recruitment accounts on Blued and prioritize outreach efforts at pilot universities—institutions identified through surveillance data as having historically higher HIV prevalence rates and larger student MSM populations.

Leveraging Blued’s geolocation features, volunteers will target MSM individuals within their assigned university campuses. Given Blued’s explicitly MSM user base, recruitment through this channel is expected to contribute at least 50% of the total sample size. To ensure consistency in intervention delivery, all participants recruited through Blued will also be required to add the corresponding volunteer’s WeChat account, through which the subsequent online intervention activities will be administered.

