### Outcome Measures

#### Primary Outcome

HIV and syphilis incidence rate: The primary outcome is the change in HIV and syphilis incidence rates before and after the intervention, assessed by comparing the postintervention incidence with the baseline incidence among local student MSM populations.

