#### Secondary Outcomes

Secondary outcome measures include (1) changes in sexual behaviors (eg, condom use, number of sexual partners) before and after the intervention; (2) frequency of biomedical intervention utilization (eg, HIV testing, STI testing, PEP, PrEP use); and (3) changes in HIV and STI prevention knowledge and awareness levels.

Detailed definitions of outcome indicators, measurement methods, and data sources are summarized in Table 1.

**Table 1. T1:** Indicators of study outcomes.

Domain	Specific indicator	Definition	Data source
Primary outcomes			
HIV incidence	Comparison between intervention cohort and local student MSM attending university	New HIV cases confirmed by medical institutions per 100 person-years vs surveillance data (2025)	Laboratory reports at 12-month follow-up; CDC^b^ surveillance data
Syphilis incidence	Comparison between intervention cohort and local student MSM attending university	New syphilis cases confirmed by medical institutions per 100 person-years vs surveillance data (2025)	Laboratory reports at 12-month follow-up; CDC surveillance data
Secondary outcomes			
Behavioral Changes			
Risk behaviors	Condom use during anal intercourse Commercial sex engagement Multiple partners	% reporting “always use condoms” in past 3 months % reporting paid sex in past 3 months % with ≥2 sexual partners in past 3 months	Structured questionnaire
Substance use	Psychoactive substance use during sex	% reporting use of chemsex drugs in past 3 months	Structured questionnaire
Testing behaviors	HIV testing frequency STI^c^ screening	% tested for HIV in past 3 months % tested for STIs in past 3 months	Structured questionnaire
Biomedical uptake			
Prevention tools	Condom/lubricant use PrEP^d^/PEP^e^ utilization	% using condom/lubricant % PrEP/PEP initiations	Supply logs; pharmacy data
Attitudinal changes			
Prevention intention	Future condom use intent Testing willingness	% planning to use condoms % willing to undergo future HIV/STI tests	Structured questionnaire
Awareness changes			
Health literacy	PEP/PrEP knowledge HIV/STIs awareness	% correctly describing PEP/PrEP protocols % choosing the right core knowledge about HIV/STIs	Knowledge assessment

a MSM: men who have sex with men.

b CDC: Centers for Disease Control and Prevention.

c STI: sexually transmitted infection.

d PrEP: preexposure prophylaxis.

e PEP: postexposure prophylaxis.

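### The primary HIV and syphilis comparison has no single comparator: the self-controlled reading cannot be estimated for HIV incidence, and the 80% power depends on comparator person-years that are not stated

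*Protocol article*

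**What the plan says.** The protocol article describes the comparison behind the primary outcome in several places.

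- **Study Design** adopts a before-after self-controlled cohort, "allowing participants to serve as their own controls to assess within-person changes". The Abstract uses the same label.
- **Primary Outcome** defines a before-to-after change in HIV and syphilis incidence, "assessed by comparing the postintervention incidence with the baseline incidence among local student MSM populations".
- **Table 1** (under Secondary Outcomes) defines the HIV indicator as "New HIV cases confirmed by medical institutions per 100 person-years vs surveillance data (2025"), and words the syphilis indicator in the same way.
- **The limitations text in the Discussion** describes the Chengdu student MSM surveillance as contemporaneous and offers it as mitigation for having no concurrent control group.

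Other parts of the article bear on these statements.

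- **Inclusion Criteria** require "confirmed HIV-negative status at baseline screening". The testing overview repeats that only men who test HIV-negative at baseline can enrol.
- **Study Setting** places the study between June 2025 and June 2026.
- **Sample Size** says "we adopted the 2-sample Poisson rate comparison framework" and takes its reference rate from a further source: "We assumed a baseline HIV incidence of 4 per 100 person-years (estimated from multiple MSM cohort studies in China"). All 484 participants are recruited into one intervention cohort.
- **Study Aims** speak of "lowering the prevalence of HIV and other STIs within this population".
- **Recruitment via Blued** prioritises "institutions identified through surveillance data as having historically higher HIV prevalence rates and larger student MSM populations".

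**The concern.** Own controls, an earlier local rate and a 2025 surveillance rate answer different questions. The first asks whether the same men changed. The second asks whether the cohort did better than local student MSM did before the intervention. The third asks whether it did better than local student MSM during roughly the same period. Only the third offers some protection against a secular trend, and the article itself reports a steep one.

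If the comparator is settled after infections have been counted, the primary conclusion can depend on that choice. The stated power is affected too, because a two-sample calculation has a second sample whose size must be known before the power means anything.

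**Working it through.** **1. Is a self-controlled HIV comparison possible?** Every participant is HIV-negative at entry by rule, and the first study test is at entry. The cohort therefore has no observed pre-intervention person-time in which an HIV infection could be counted, and there is no before rate. Syphilis does not require a negative baseline, but no pre-entry person-time is observed for it either. The questionnaire outcomes are measured at baseline, 6 and 12 months, and can be self-controlled. For the same reason, HIV prevalence inside the cohort starts at zero and cannot fall.

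**2. Does 2025 surveillance fit either of the other descriptions?** The study runs from June 2025 to June 2026. Data for 2025 overlap the intervention, so they are not a pre-intervention baseline. They omit the 2026 part of follow-up, so they are not fully concurrent.

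**3. Reproducing 484.** Inputs from Sample Size: rates 0.04 and 0.01 per person-year, two-sided α 0.05, 80% power, 10% attrition. Equal groups with one year per person are my assumption.

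- Person-years (PY) per group = (z₀.₉₇₅ + z₀.₈₀)² × (λ₀ + λ₁) / (λ₀ − λ₁)² = (1.960 + 0.842)² × 0.05 / 0.03² = 436.05.
- Allowing for attrition: 436.05 / 0.9 = 484.5, against 484 stated.

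The stated figure is therefore the size of one group. Two enrolled groups would need 2 × 484.5 ≈ 969.

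**4. Power as a function of the unstated comparator size.** The cohort contributes 484 × 0.9 = 435.6 PY. The first five rows use the normal approximation with pooled variance for 4 versus 1 per 100 PY.

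| Comparator PY (assumed) | Power |
|---|---|
| 200 | 67% |
| 300 | 74% |
| 436 | 80% |
| 1000 | 90% |
| 2000 | 95% |
| Reference rate treated as fixed (exact Poisson, reject if X ≤ 9, lower tail 0.0209) | 98.6% |

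**5. Can the reference period decide the result?** Sample Size reports a 60.9% fall in new HIV infections in Chengdu MSM between 2022-2023 and 2023-2024. As an illustration only, apply a fall of that size to the planning rate: 4 × (1 − 0.609) = 1.56 per 100 PY. Treat both reference rates as fixed, with 435.6 cohort PY.

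- Expected infections: 435.6 × 0.04 = 17.4 and 435.6 × 0.0156 = 6.8.
- Against 17.4: P(X ≤ 9) = 0.021 and P(X ≤ 10) = 0.040, so counts up to 9 are significant at a lower tail of 0.025.
- Against 6.8: P(X ≤ 1) = 0.009 and P(X ≤ 2) = 0.035, so only counts of 0 or 1 are significant.

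Any count from 2 to 9 is significant against the first rate and not the second. The planned rate of 1 per 100 PY gives 435.6 × 0.01 = 4.4 expected infections, inside that range. A count of 4, for example, has a lower tail of 0.0001 against one rate and 0.19 against the other.

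**The case against.** The strongest reply is that the conflict is narrower than it looks. The Study Design sentence is a general label. The two places that define the primary outcome both point to local student MSM, and the Discussion confirms an external surveillance comparison. On that reading the defect is one timing conflict (baseline or 2025) plus a loose label. This is largely fair, but it does not settle the comparator: a baseline and a calendar year that overlaps the intervention are different references, and the self-controlled label is attached to the whole design.

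A reader might infer several stronger things that the documents do not support.

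- **That 484 is half of what is needed, or that the second group's person-years will never exist.** Table 1 names CDC surveillance as the second source. If it supplies about 436 PY or more, enrolling 484 is enough for the stated power. The equal-group reading is also inferred from the reproduction, because the appendix with the derivation is not shown.
- **That the secular change exceeds any plausible intervention effect.** A 60.9% fall is a factor of 1/0.391 = 2.56, and the plan itself assumes a factor of 4. The reported fall concerns new infections in Chengdu MSM overall in earlier periods. It is not stated to be a rate, or to concern students or 2025. It shows that adjacent periods can differ substantially, not by how much they will.
- **That the cohort comes from high-prevalence campuses.** Only the Blued outreach prioritises them, and Blued is expected to supply at least half of the sample. No such targeting is stated for WeChat. A mismatch with a general student MSM rate is possible, but its size is unknown.
- **That the whole prevalence aim is unattainable.** Other infections need not be absent at entry; the point applies to HIV only.

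The Discussion also promises sensitivity analyses for secular trends, cautious reading of incidence and reliance on behavioural outcomes. These soften the consequences but do not say which comparison is primary.

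**Conclusion.** The point holds as a contradiction in how the primary comparison is fixed. The HIV part of a self-controlled incidence comparison cannot be estimated, and the two external descriptions disagree on period. An unseen analysis plan would have to override at least one of these statements, so this is not merely detail left out of an article.

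On the illustrative rates of 4 and 1.56 per 100 PY, treated as fixed, the choice of reference reverses significance for every count from 2 to 9. The size of that window rests on borrowing the 60.9% fall; the dependence on the reference period does not.

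The 484 is reproduced and is not shown to be wrong or underpowered. Its 80% power is conditional on about 436 comparator PY. Over comparator sizes of 200 to 2000 PY the power runs from 67% to 95%, and it is 98.6% against a fixed rate.

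**What to change.** Before any outcome data are seen:

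1. Name one primary comparison: infections observed in the cohort against infections expected from Chengdu student MSM surveillance over the same calendar months as follow-up, through June 2026. Standardise to age and to the enrolling universities where the surveillance data allow it.
2. Report the ratio with an interval that includes the comparator's own count uncertainty, rather than treating the surveillance rate as known.
3. Bring Study Design, Primary Outcome and Table 1 into line with that comparison, and keep the self-controlled label for the questionnaire outcomes only.
4. In Study Aims, use incidence rather than prevalence for HIV.
5. State the comparator person-years and restate the power from them.

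The cost is mainly wording and a tabulation of surveillance data that the study already plans to use. The primary outcome loses the self-controlled label, and the analysis must wait for 2026 surveillance. Standardising by university needs campus-level numerators and denominators that the article does not show to exist; if they are unavailable, the possible campus mismatch should be stated as a limitation.

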#### Secondary Outcomes

Secondary outcome measures include (1) changes in sexual behaviors (eg, condom use, number of sexual partners) before and after the intervention; (2) frequency of biomedical intervention utilization (eg, HIV testing, STI testing, PEP, PrEP use); and (3) changes in HIV and STI prevention knowledge and awareness levels.

Detailed definitions of outcome indicators, measurement methods, and data sources are summarized in Table 1.

**Table 1. T1:** Indicators of study outcomes.

Domain	Specific indicator	Definition	Data source
Primary outcomes			
HIV incidence	Comparison between intervention cohort and local student MSM attending university	New HIV cases confirmed by medical institutions per 100 person-years vs surveillance data (2025)	Laboratory reports at 12-month follow-up; CDC^b^ surveillance data
Syphilis incidence	Comparison between intervention cohort and local student MSM attending university	New syphilis cases confirmed by medical institutions per 100 person-years vs surveillance data (2025)	Laboratory reports at 12-month follow-up; CDC surveillance data
Secondary outcomes			
Behavioral Changes			
Risk behaviors	Condom use during anal intercourse Commercial sex engagement Multiple partners	% reporting “always use condoms” in past 3 months % reporting paid sex in past 3 months % with ≥2 sexual partners in past 3 months	Structured questionnaire
Substance use	Psychoactive substance use during sex	% reporting use of chemsex drugs in past 3 months	Structured questionnaire
Testing behaviors	HIV testing frequency STI^c^ screening	% tested for HIV in past 3 months % tested for STIs in past 3 months	Structured questionnaire
Biomedical uptake			
Prevention tools	Condom/lubricant use PrEP^d^/PEP^e^ utilization	% using condom/lubricant % PrEP/PEP initiations	Supply logs; pharmacy data
Attitudinal changes			
Prevention intention	Future condom use intent Testing willingness	% planning to use condoms % willing to undergo future HIV/STI tests	Structured questionnaire
Awareness changes			
Health literacy	PEP/PrEP knowledge HIV/STIs awareness	% correctly describing PEP/PrEP protocols % choosing the right core knowledge about HIV/STIs	Knowledge assessment

a MSM: men who have sex with men.

b CDC: Centers for Disease Control and Prevention.

c STI: sexually transmitted infection.

d PrEP: preexposure prophylaxis.

e PEP: postexposure prophylaxis.

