### Study Setting

This study is scheduled to commence in June 2025 and conclude in June 2026. The research process will consist of the following sequential phases: participant recruitment, HIV/hepatitis C virus (HCV)/hepatitis B surface antigen (HBsAg)/syphilis testing, baseline survey, intervention implementation, midterm survey, and final follow-up survey.

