## Results

Participant enrollment and data collection are currently ongoing. This trial protocol has been developed in accordance with the SPIRIT (Standard Protocol Items: Recommendations for Interventional Trials) 2013 guidelines [27].

As of May 1, 2025, the intervention materials and training program have been finalized, and recruitment has begun. Enrollment of participants started in April 2025. By the end of April, 127 participants had completed baseline surveys and HIV/STI self-tests.

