### Data Collection and Baseline Assessment: Ensuring Reliability of Self-Reported Data

The baseline survey collects sensitive data, including sexual behaviors, substance use, and HIV-related risk factors. Due to social desirability bias or privacy concerns, participants may underreport or misreport behaviors, potentially affecting data accuracy.

To address this, volunteers will emphasize the project’s strict confidentiality protocols when inviting participants to complete the questionnaire. Participants will be clearly informed that no PII is collected in the survey, all data are securely stored in the back-end system, and only the project manager has access to detailed records.

This study has limitations. The before-after self-controlled cohort design does not include a concurrent control group, which limits the ability to make causal inferences. However, a randomized controlled trial was not feasible due to ethical and operational considerations—specifically, the local ethics committee’s recommendation that all eligible university students should have access to the intervention resources. To mitigate this limitation, we will compare changes observed in this study with contemporaneous surveillance data from the Chengdu student MSM population, conduct sensitivity analyses to assess secular trends, and interpret outcomes cautiously in light of these contextual factors. Despite these constraints, the design remains appropriate for evaluating real-world implementation and effectiveness under routine public health conditions. While the assumed reduction in incidence may be optimistic, behavioral indicators such as HIV testing and PEP/PrEP uptake serve as sensitive early markers of intervention impact in this short-term cohort. Given the expected rarity of incident infections over 12 months in student MSM cohorts, we interpret incidence changes cautiously while relying on proximal behavioral outcomes with higher short-term sensitivity.

By proactively addressing these anticipated challenges through standardized training, robust recruitment and retention strategies, and comprehensive privacy protections, this study aims to ensure rigorous implementation while generating valuable insights into the feasibility and effectiveness of internet-based, peer-led HIV prevention interventions among university student MSM.

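### Three passages name three different comparators for the primary outcome, and the one in Table 1 (2025) sits about 3 to 6 months earlier than the cohort's follow-up

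*Protocol article*

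**What the plan says.** The protocol article describes the comparator for the primary outcome in three places.

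- **Primary Outcome section:** the change is assessed by "comparing the postintervention incidence with the baseline incidence among local student MSM populations".
- **Table 1 (Secondary Outcomes section), presented as the detailed definitions:** the HIV row reads "New HIV cases confirmed by medical institutions per 100 person-years vs surveillance data (2025"). The syphilis row has the same form and the same year.
- **Limitations text (end of the Discussion):** "we will compare changes observed in this study with contemporaneous surveillance data from the Chengdu student MSM population, conduct sensitivity analyses to assess secular trends".

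On timing, Study Design says that "this study will set a 12-month intervention duration, with an interim follow-up assessment at 6 months". Study Setting says "This study is scheduled to commence in June 2025 and conclude in June 2026", while Results reports that "Enrollment of participants started in April 2025".

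On trend, the Sample Size section reports a 60.9% year-over-year fall in new HIV infections among Chengdu MSM between 2022-2023 and 2023-2024, and bases its planning effect partly on it.

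On population, Recruitment via Blued gives priority to "institutions identified through surveillance data as having historically higher HIV prevalence rates and larger student MSM populations", and that channel is expected to supply at least half of the sample.

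**The concern.** The study has no concurrent control group, so the primary inference rests on the external rate. The three descriptions of that rate do not agree. A baseline rate suggests a period before the intervention. The year 2025 overlaps the intervention but stops before follow-up ends. A contemporaneous rate would run to the end of follow-up. Left open, the choice could be made after the rates are known.

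Following Table 1 as written also compares later person-time with an earlier reference period. If incidence is falling for reasons unrelated to the intervention, the later cohort will look better even when the intervention does nothing.

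**Working it through.** **Reproducing the plan's own figure.** Inputs from Sample Size: 4 versus 1 per 100 person-years, two-sided alpha .05, 80% power, 10% attrition. With a normal approximation to the two-sample Poisson comparison:

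n = (1.960 + 0.842)² × (0.04 + 0.01) / (0.04 − 0.01)² = 436.05 person-years per period; 436.05 / 0.9 = 484.5.

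This agrees with the stated 484, so the planning rates are read correctly here.

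**Offset between comparator and follow-up.** Table 1 says only 2025; I read it as the calendar year, centred near 1 July 2025. A 12-month follow-up is centred six months after its start. The offset t therefore equals the time from 1 January 2025 to the start of follow-up, and t in years is also the share of follow-up that falls in 2026. Start dates run from April 2025 (Results) to June 2025 (Study Setting).

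**Trend-only reduction.** With a constant proportional decline d per year and no intervention effect, the apparent reduction is 1 − (1 − d)^t. For a start on 1 April, t = 90/365 = 0.247 and 1 − 0.391^0.247 = 20.7%. For 30 June, t = 180/365 = 0.493 and 1 − 0.391^0.493 = 37.1%.

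| Start of follow-up | Offset (months) | Follow-up in 2026 | d = 60.9% | d = 31.5% | d = 20% | d = 10% |
|---|---|---|---|---|---|---|
| 1 April | 2.96 | 25% | 20.7% | 8.9% | 5.4% | 2.6% |
| 15 April | 3.42 | 28% | 23.5% | 10.2% | 6.2% | 3.0% |
| 1 May | 3.95 | 33% | 26.6% | 11.7% | 7.1% | 3.4% |
| 1 June | 4.96 | 41% | 32.2% | 14.5% | 8.8% | 4.3% |
| 15 June | 5.42 | 45% | 34.6% | 15.7% | 9.6% | 4.7% |
| 30 June | 5.92 | 49% | 37.1% | 17.0% | 10.4% | 5.1% |

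Only the 60.9% is a trend reported in the document. The slower declines are assumptions chosen to show the range, and d = 0 gives zero. If the baseline rate in the Primary Outcome section means a period a full year earlier, t = 1 and the 60.9% trend would pass through in full.

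**What drift of this size could do to a test (illustration).** Assume 436 person-years, a 2025 rate of 4 per 100 taken as known, and an exact lower-tail test at .025, which rejects at 9 or fewer cases. An inert intervention would be declared effective with probability 2.1% under no drift, about 15% under a 24% drift and about 31% under a 35% drift. If the comparator is itself estimated from 436 person-years, the figures are 2.5%, about 11% and about 21%.

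**The case against.** The strongest reply is that the limitations text already promises contemporaneous surveillance, sensitivity analyses for secular trends and cautious reading of incidence. The protocol as a whole therefore does not commit to 2025, and details may sit in an analysis plan that is not shown. This is fair as far as it goes. But a sensitivity analysis leaves the primary definition unchanged, and the conflict lies between statements in the article itself. It is not a detail deferred to another document.

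A reader might infer that the Table 1 comparator would in itself produce a spurious reduction of 24-35%. The documents do not support that. The arithmetic is right for mid-April to mid-June starts, but only if the 60.9% decline recurs through mid-2026. That figure is one past change, in new infections not stated to be a rate, among all Chengdu MSM and not students. A reader might also infer that drift generally reaches the 31.5% benchmark effect cited under Sample Size. In the table, only the June starts at the full 60.9% do so.

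Two further points stand. Between 51% and 75% of follow-up does lie within 2025, so the mismatch is partial. And including participants in the surveillance rate matters little: 484/8401 = 5.8% overlap, using the 2021 estimate of student MSM in the Introduction. At the planning rates the comparator becomes 0.942 × 4 + 0.058 × 1 = 3.83 per 100, and the rate ratio moves from 0.25 to 0.26, slightly against the intervention.

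**Conclusion.** The point holds as an inconsistency with a calendar mismatch. Three passages give three comparators, and the Table 1 version leaves an offset of about 3 to 6 months in both primary rows. The direction is towards apparent benefit if HIV incidence is still falling. The size is conditional: about 21-37% at a continued 60.9% annual decline, 3-17% at assumed declines of 10-31.5%, and none without a trend. It rests on reading 2025 as the calendar year, on a constant proportional decline, and on follow-up starting between April and June 2025.

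These sizes cannot be carried over to syphilis, for which the documents give no trend. Nor can the net bias be signed with confidence: priority for higher-prevalence universities may raise the cohort's rate relative to all local student MSM, by an amount that the documents do not give.

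**What to change.** Reconcile the Primary Outcome section, both primary rows of Table 1 and the limitations text to one primary comparator: surveillance incidence among local student MSM over the same calendar months as cohort follow-up, with the extract running to the end of follow-up in 2026. Restrict it to the recruiting universities and exclude participants where the surveillance data allow. Report calendar 2025 and pre-intervention rates as context only. Settle this before the 2026 rates are seen.

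Finer standardisation by month or age group is not needed. The planning rates imply only about 4 to 17 HIV cases (436 × 0.01 = 4.4; 436 × 0.04 = 17.4).

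The cost is a consistent edit in three places, a longer surveillance extract, and the wait for the 2026 data. Recruitment and the intervention are unaffected. The documents do not say whether surveillance can be split by university or linked to participants, so those two refinements stay conditional.
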